### Sample size

All 221 children from the VICS cohort will be invited to participate in the trial providing that they fit the eligibility criteria for this study. We conservatively estimate that approximately 60% of the VICS cohort will be eligible and will consent to participate in the trial, which will provide a sample size of 126 for this study (63 per treatment group; Figure 2). A participation rate of 60% allows for children who will not be seen through the VICS follow-up (10%), as well as children who do not meet the eligibility criteria (5%; approximately n= 11). A sample size of 63 in each group will enable us to detect an increase in our primary outcome, academic functioning (such as mathematics) 24 months' post-intervention, of 0.5 SD in the intervention compared with the placebo group, with 80% power and a type-I error rate of 5%. An increase of 0.5 SD in academic outcomes is the improvement seen following Cogmed in other populations after 6 months and would be a clinically important difference to detect [39]. Of the 126 participants, we expect approximately 80% to consent to the neuroimaging component of the study, thus a sample size of 100 (50 per group) to assess the secondary objective regarding neuroplasticity. A sample size of 50 in each group with neuroimaging data will enable us to detect differences of 0.57 SD in measures of neuroplasticity (i.e. percentage BOLD signal change between pre-intervention and 2-weeks’ post-intervention for fMRI analyses, and tract volume, FA or AD for DWI analyses), with 80% power and a type-I error rate of 5%.

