Evidence supporting Cogmed was initially obtained from studies involving children with ADHD. A randomised controlled trial (RCT) of 53 children with ADHD revealed evidence of improved outcomes immediately and 3 months’ post-intervention in non-trained working memory tasks, inhibitory control, problem solving, and inattention and hyperactivity/ impulsivity symptoms compared with a placebo (non-adaptive) program (a program that included the same activities as the adaptive program but set at a lower difficulty level that does not increase progressively) [36]. These findings suggest that benefits associated with Cogmed were transferred to other aspects of cognitive functioning and everyday behaviour. Benefits of Cogmed have also been reported in other populations. In an un-blinded, non-randomised, school-based study of school-aged children assessed to have “low working memory capacity”, Holmes and colleagues [39] found that children who trained with Cogmed demonstrated long-term improvements in working memory, while children exposed to the placebo program exhibited only marginal improvements in working memory. By 6 months’ post-intervention, adaptive training was associated with an improvement in mathematical reasoning compared with pre-training baseline levels (mean difference of 0.5 SD). A more recent randomised, placebo-controlled (non-adaptive and no intervention groups) trial conducted within the school setting, replicated the benefit of adaptive training on a range of untrained working memory tasks. However, selective enhancement on academic attainment and other cognitive skills was not found either immediately after training or 1 year later [40].

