### Randomisation

Prior to the Cogmed start-up session , the child will be randomised to either the adaptive working memory training program (intervention) group or the non-adaptive working memory training program (placebo) group in a 1:1 ratio. A biostatistician who is independent of the study will generate the randomisation schedule using block randomisation with variable block sizes. Randomisation will be stratified by singleton versus multiple births (twins/triplets) and ‘low’ versus ‘age-typical’ working memory capacity at baseline (total of 4 strata), to ensure equal allocation of these factors across the 2 treatment arms. For this trial, “low” working memory capacity will be classified as performing less than or equal to the 20th percentile on the Backward Digit Recall subtest from the Working Memory Test Battery for Children (WMTB-C) [63]. Approximately 40% of participants will be classified as ‘low’ working memory, based on recently published data from a 7 year follow-up study carried out by the Victorian Infant Brain Studies (VIBeS) group [64]. Twins and triplets (approximately 23%) will be allocated to the same intervention group to reduce contamination.

Randomisation will be conducted via opaque envelopes managed by the project co-ordinator and research assistant. Participants will be allocated the next available sequential study number in the required strata and this corresponds to an envelope which will contain the allocation to intervention or placebo group. The project co-ordinator or research assistant will open the envelope to obtain the treatment allocation either on the morning of the Cogmed start-up session or the night before, depending on the time and location of the session. The participant and their family will remain blinded to the assigned treatment allocation throughout the study. Other than the project co-ordinator and research assistant, all other members of the trial team will also remain blinded to treatment allocation throughout the study.

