### Statistical analysis

All analyses will be carried out using an intention-to-treat approach, including all participants as randomised. Analysis will be carried out on those with outcome data available. Summaries of all primary and secondary outcomes will be presented by treatment group. Results will be presented as means and SDs of age standardised scores for continuous outcomes, and numbers and proportions for categorical variables. Differences between the groups on continuous outcomes will be assessed using linear regression adjusted for stratification factors of multiple births and low/normal working memory capacity at baseline. Models will be fitted using generalised estimating equations (GEEs) to allow for clustering of multiples, with results presented as the mean difference and 95% confidence intervals (CIs) calculated from sandwich estimates of standard errors. As a sensitivity analysis, results will also be adjusted for any other baseline factors where there is a chance imbalance between the 2 groups using linear regression. Differences between groups on binary outcomes will be assessed using logistic regression adjusted for stratification factors of multiple births and low/normal working memory capacity at baseline, again fitted using GEEs. Results will be presented as odds ratios (ORs) and 95% CIs calculated using sandwich estimates of standard errors. Due to the issues of multiple testing, results will be interpreted according to magnitude of the group difference rather than relying solely on significance levels. Compliance and motivation data will be presented descriptively by treatment arm.

For the fMRI data, the effects of group, time (pre-intervention and 2 weeks’ post-intervention) and task (0-back and 1-back conditions) will be examined using factorial analyses by fitting an analysis of variance (ANOVA) model [81]. fMRI effective connectivity will be examined using Dynamic Causal Modelling [82].

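### The 80% power for a 0.5 SD difference at 24 months leaves out both loss to follow-up and same-arm twins, and the cited basis for 0.5 SD is a within-group gain

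*Protocol article*

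**What the plan says.** The Sample size section states: "A sample size of 63 in each group will enable us to detect an increase in our primary outcome". The increase meant is a 0.5 SD difference between intervention and placebo in academic functioning at 24 months, with 80% power and 5% type I error. The recruitment figure allows for 10% of the cohort not being seen at the 7-year visit and 5% being ineligible. Both act before enrolment.

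Three other statements bear on that figure:

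- Statistical analysis: "Analysis will be carried out on those with outcome data available". The same section adjusts for multiple birth and for low/normal baseline working memory, and fits the models by GEE to allow for clustering of multiples.
- Randomisation: "Twins and triplets (approximately 23%) will be allocated to the same intervention group to reduce contamination".
- On the size of the target, Sample size says "An increase of 0.5 SD in academic outcomes is the improvement seen following Cogmed in other populations after 6 months", and adds that it would be clinically important. The Background describes the same cited study as un-blinded and non-randomised, and its result as an "improvement in mathematical reasoning compared with pre-training baseline levels (mean difference of 0.5 SD").

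**The concern.** The power statement matches a simple two-sample calculation with nothing held in reserve. Two features of the design reduce the information below that. Children without a 24-month score drop out of the analysis. Siblings in the same arm do not contribute as two independent children. The analysis section recognises the clustering, but the sample size section does not.

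A further weakness is the support given for 0.5 SD. A gain from children's own baseline includes maturation, practice and regression to the mean, which a placebo arm would share. It therefore does not indicate how large a difference from placebo to expect. The Background also reports a randomised placebo-controlled trial that found no selective academic gain, either immediately or at 1 year.

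At stake is how a null result is read. Anyone relying on the planning statement would credit the trial with 80% power for 0.5 SD, without seeing what that figure assumes.

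**Working it through.** **Inputs from the protocol.** 63 per arm, 1:1 allocation, difference 0.5 SD, alpha 5% (taken as two-sided, which reproduces the plan's number), 23% multiples in the same arm, about 40% classed as low working memory. The Background gives correlations of 0.42 to 0.61 between verbal working memory and academic achievement in very preterm children.

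**Inputs not in the protocol (assumptions).** Loss between randomisation and 24 months: 10% and 20%. Sibling correlation ρ in the outcome: 0.5 to 0.7. The 10% echoes the non-attendance the plan expects for the whole cohort at age 7, which is a different population and period.

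**1. The plan's own figure.** Power = P(T > t₀.₉₇₅), where T is noncentral t with 2n − 2 degrees of freedom and noncentrality δ√(n/2). With n = 63 and δ = 0.5, power is 79.5% (80.1% by normal approximation); n = 64 gives 80.1%. So 63 is the number needed with complete, independent data. No surplus sits in the recruitment figure: 221 × 0.95 ≈ 210 and 210 × 0.60 = 126.

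**2. Loss alone.** At 10%: 63 × 0.9 = 56.7 per arm, power 75.2%.

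**3. Loss and clustering.** Treating the 23% as same-arm pairs with exchangeable weighting, effective n per arm = 63 × (1 − loss) × [0.77 + 0.23/(1 + ρ)].

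- ρ = 0.5: the bracket is 0.923; at 10% loss, effective n = 52.4.
- ρ = 0.7: the bracket is 0.905; at 10% loss, effective n = 51.3.

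**4. Planned covariate.** Splitting a normal variable at its 40th percentile multiplies its correlation with the outcome by about 0.789. So 0.42 × 0.789 = 0.33 and 0.61 × 0.789 = 0.48, which give R² of 0.11 and 0.23. Adjustment replaces 0.5 by 0.5/√(1 − R²). This keeps ρ unchanged, which is a simplification.

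| Loss | ρ | Power, no covariate | Power, R² 0.11 | Power, R² 0.23 |
|---|---|---|---|---|
| 10% | 0.5 | 71.7% | 76.6% | 82.3% |
| 10% | 0.7 | 70.8% | 75.8% | 81.6% |
| 20% | 0.5 | 66.5% | 71.6% | 77.6% |
| 20% | 0.7 | 65.6% | 70.7% | 76.8% |

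At 10% loss the difference detectable with 80% power is 0.55 to 0.56 SD without covariates. Multiplying by √(1 − R²) gives about 0.49 to 0.53 SD with the covariate.

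With an independence working correlation (design effect 1 + 0.23ρ), the unadjusted figures at 10% loss are one to two points lower: 70.4% at ρ = 0.5 and 68.6% at ρ = 0.7.

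**5. Baseline WRAT-4 as covariate.** With 15% loss, ρ = 0.6 and a baseline–outcome correlation of 0.5, 0.6 or 0.7, power is 81%, 86% or 93%. At 20% loss and a correlation of 0.5 it is about 78%.

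**6. Smaller true effects.** With all 126 children independent and observed, power is 61% at 0.4 SD and 39% at 0.3 SD.

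**The case against.** The strongest reply is that the unadjusted figures describe a model the protocol does not plan to fit. The primary comparison adjusts for baseline working memory group. Using the only correlations in the document, that adjustment recovers much of the loss, and the resulting range includes 80%. This stands, and it is why the adjusted columns belong beside the unadjusted ones. It rests in turn on the Background correlations carrying over to an outcome two years later, and the sample size section claims no such gain.

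The loss rate and sibling correlation are assumed. Families were screened for their ability to support the child through training, so loss may be below 10%. Some multiples may have no enrolled sibling, which would reduce the clustering. This also stands: the omission is certain, its size is not.

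On the effect size, a reader might infer that the protocol presents 0.5 SD as an observed difference from placebo. It does not. It calls it an improvement seen after Cogmed, reports the source's weak design openly, and separately calls 0.5 SD clinically important. What remains is that a between-group target is supported by a within-group figure.

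Finally, results are to be reported with confidence intervals and interpreted by magnitude. That limits the harm to the reading of a null result but does not correct the stated power.

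**Conclusion.** The concern holds as a should-fix. The stated 80% requires 126 independent children all observed at 24 months, and the protocol's own design meets neither condition. Under the assumptions shown, power for 0.5 SD is about 71% to 72% unadjusted and 76% to 82% adjusted at 10% loss, or about 66% and 71% to 78% at 20% loss.

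A reader might conclude that the trial lacks its stated power. The documents do not establish that: with modest loss and a covariate at the upper end of the range, the planned analysis reaches 80%. What is established is that the stated calculation has no margin and omits two known features of the design. The 0.5 SD can stand as a target difference, but the cited gain is not evidence that an effect of that size against placebo should be expected.

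**What to change.** Keep the sample size; the source cohort is fixed at 221. Reword the Sample size paragraph to:

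- give the number expected with 24-month WRAT-4 data, the assumed sibling correlation for the 23% multiples, and the variance the stratification covariates are assumed to explain, each with a range;
- state the resulting power, or the difference detectable with 80% power, for the planned adjusted GEE analysis;
- justify 0.5 SD as the clinically important target, and note that the cited 0.5 SD was a change from baseline in a non-randomised study.

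Power at 0.3 and 0.4 SD would be a useful addition. The cost is rewording and a figure that may look less favourable.

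Optionally, add baseline WRAT-4, already collected according to Table 1, to the primary model. This brings power to about 80% or more if its correlation with the outcome is at least 0.5 and loss is no more than about 15%. It changes the primary analysis, so it should be adopted only by an amendment made before unblinded outcome data are seen.

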**Figure 2 F2:**
[figure not shown]
Flowchart of study participants.

### Statistical analysis

All analyses will be carried out using an intention-to-treat approach, including all participants as randomised. Analysis will be carried out on those with outcome data available. Summaries of all primary and secondary outcomes will be presented by treatment group. Results will be presented as means and SDs of age standardised scores for continuous outcomes, and numbers and proportions for categorical variables. Differences between the groups on continuous outcomes will be assessed using linear regression adjusted for stratification factors of multiple births and low/normal working memory capacity at baseline. Models will be fitted using generalised estimating equations (GEEs) to allow for clustering of multiples, with results presented as the mean difference and 95% confidence intervals (CIs) calculated from sandwich estimates of standard errors. As a sensitivity analysis, results will also be adjusted for any other baseline factors where there is a chance imbalance between the 2 groups using linear regression. Differences between groups on binary outcomes will be assessed using logistic regression adjusted for stratification factors of multiple births and low/normal working memory capacity at baseline, again fitted using GEEs. Results will be presented as odds ratios (ORs) and 95% CIs calculated using sandwich estimates of standard errors. Due to the issues of multiple testing, results will be interpreted according to magnitude of the group difference rather than relying solely on significance levels. Compliance and motivation data will be presented descriptively by treatment arm.

For the fMRI data, the effects of group, time (pre-intervention and 2 weeks’ post-intervention) and task (0-back and 1-back conditions) will be examined using factorial analyses by fitting an analysis of variance (ANOVA) model [81]. fMRI effective connectivity will be examined using Dynamic Causal Modelling [82].

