**Table 1 T1:** **Outcome measures and study time**-**points**

**Outcome measures**			**Time-point**^**#**^			
			**Baseline***	**2 week**	**12 month**	**24 month**
**Academic achievement**	Wide Range Achievement Test-4th edition (WRAT-4)	Child	•	•	•	•
	Academic performance questionnaire	Parent	•	•	•	•
		Teacher	•			•
**Working memory**	Working Memory Test Battery for Children (WMTB-C)	Child	•	•	•	•
	Automated Working Memory Assessment (AWMA)	Child	•	•	•	•
**Attention**	Test of Everyday Attention for Children (TEACh)	Child	•	•	•	•
**Speed of processing**	CogState	Child	•	•	•	•
**General Cognitive ability**	Differential Ability Scale-2nd edition (DAS-II)	Child	•			
**Behaviour**	Strength & Difficulties Questionnaire (SDQ)	Parent	•	•	•	•
		Teacher	•			•
	Behavior Rating Inventory of Executive Function (BRIEF)	Parent	•	•	•	•
		Teacher	•			•
	Cogmed Training Evaluation Scales	Parent	•	•		
**Motivation**	Intrinsic Motivation Scale	Child	•			
	Intrinsic Motivation Inventory	Child		•		
**Neuroimaging**	MRI	Child	•	•		

^#^The presence of the ‘•’ symbol in Table 1 indicates when an outcome measure will be collected at a specific time-point from either a child or parent/teacher.

^*^Neuropsychological measures and behavioural questionnaires at the baseline time-point were completed prior to enrolment into the trial as part of a regional follow-up program.

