#### Primary outcome

The primary outcome of the study is academic achievement 24 months’ post-intervention as measured using the Wide Range Achievement Test -4th edition (WRAT-4) [65]. The WRAT-4 includes subtests that assess reading (single word decoding), sentence comprehension, spelling, and math computation. Each scale is age standardised with a mean of 100 and SD of 15. Secondary information regarding literacy and numeracy, academic performance, grade repetition, and integration assistance will be sought from parents and teachers through an academic performance questionnaire.

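### The primary model omits the baseline WRAT-4 score, giving up precision in a trial whose source cohort is fixed

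*Protocol article*

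**What the plan says.** The Statistical analysis section of the protocol article fixes the covariates for all continuous outcomes: "linear regression adjusted for stratification factors of multiple births and low/normal working memory capacity at baseline". The model is fitted by GEE with sandwich standard errors to allow for siblings. Other baseline variables appear only as a sensitivity analysis, in which "results will also be adjusted for any other baseline factors where there is a chance imbalance between the 2 groups". No criterion for imbalance is given.

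The primary outcome is the WRAT-4 at 24 months, and "Each scale is age standardised with a mean of 100 and SD of 15". Table 1 marks the WRAT-4 at baseline, 2 weeks, 12 months and 24 months. The footnote to the table says that the baseline neuropsychological measures were completed before enrolment, as part of the regional follow-up. They therefore precede randomisation.

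Under Randomisation, the working-memory stratum is one subtest, Backward Digit Recall, cut at the 20th percentile, with about 40% of children expected to fall in the low group. Under Sample size, all 221 cohort children are to be invited, and 63 per arm is set to detect 0.5 SD with 80% power at a 5% type-I error rate.

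**The concern.** A child's earlier score on the same achievement test would be expected to predict the later score well. The planned model instead relies on a dichotomised score from one working-memory subtest, which measures a different construct. Adding the baseline score would need no extra visit and no extra child. The cohort is fixed and every member is already being invited, so recruitment offers little room to make up precision.

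The sensitivity analysis does not fill the gap. It admits baseline WRAT-4 only when the arms look different on it, so covariates are chosen after the randomised groups have been seen, and for imbalance instead of prognosis. It leaves the primary estimate no more precise and can place a second, data-selected estimate beside it.

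**Working it through.** **The plan's own figure.** With a 0.5 SD difference, two-sided 5% and 80% power, n per arm = 2(1.960 + 0.842)²/0.5² = 62.8, so 63. Power at 63 per arm is 80.1% by the normal approximation and 79.5% by the noncentral t. The stated figure reproduces, for a comparison with no covariates.

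**What the planned model already gains.** The Background reports correlations of 0.42 to 0.61 between verbal working memory and academic achievement in very preterm children. Assume that these apply to Backward Digit Recall and the WRAT-4. Cutting a normal score so that 40% are low multiplies a correlation by φ(z₀.₄)/√(0.4 × 0.6) = 0.789. The stratum then correlates with the outcome at b = 0.331 to 0.481 and explains b² = 11% to 23% of variance.

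**Adding baseline WRAT-4.** Let r be the correlation between baseline and 24-month WRAT-4 (not in the document; 0.3 to 0.7 taken here). Assume that the stratum has the same correlation b with both scores. Then

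R² = (b² + r² − 2b²r)/(1 − b²).

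Example with b² = 0.110 and r = 0.5: R² = (0.110 + 0.250 − 0.110)/0.890 = 0.281. Residual variance is 0.719 against 0.890 as planned, a ratio of 0.81.

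**A second scenario.** Assume 15% loss by 24 months and a sibling ICC of 0.5 (neither is in the document). Treat the roughly 23% of multiples as pairs, with design effect 1 + 0.5. Effective n per arm = 126 × 0.85 × (0.77 + 0.23/1.5)/2 = 49.4.

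Power for 0.5 SD is from the noncentral t, and the detectable difference at 80% power from the normal approximation. Each cell gives the result for the lower and then the upper working-memory correlation.

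| Model | Residual variance | Power, 63 per arm | Detectable difference, 63 per arm (SD) | Power, 49.4 per arm |
|---|---|---|---|---|
| Planned (stratum only) | 0.890 / 0.769 | 83.9% / 88.8% | 0.47 / 0.44 | 74.2% / 80.2% |
| Plus baseline, r = 0.3 | 0.850 / 0.762 | 85.6% / 89.0% | 0.46 / 0.44 | 76.1% / 80.5% |
| Plus baseline, r = 0.5 | 0.719 / 0.675 | 90.7% / 92.4% | 0.42 / 0.41 | 82.7% / 85.0% |
| Plus baseline, r = 0.7 | 0.499 / 0.483 | 97.6% / 98.0% | 0.35 / 0.35 | 93.6% / 94.3% |

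Against the planned model, residual variance falls by 1–5% at r = 0.3, 12–19% at r = 0.5 and 37–44% at r = 0.7.

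**Chance baseline gap.** With 63 per arm, the baseline difference between arms has a chance SD of √(2/63) = 0.178 SD. It carries into an unadjusted 24-month comparison multiplied by r: 0.178 × 0.5 = 0.09 SD, or 0.178 × 0.7 = 0.12 SD. Stratification on a correlated factor reduces this somewhat.

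**The case against.** The strongest reply is that nothing here is an error. A randomised comparison adjusted for its stratification factors is unbiased, its covariates are prespecified, the sample size reproduces, and the imbalance-driven adjustment is labelled a sensitivity analysis. All of that stands. It limits the point to efficiency and prespecification, but does not remove it. Nor is this a detail left to an analysis plan, because the article states the covariate set.

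Several stronger readings are tempting, and the document does not support them:

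- **That the gain starts from a model with no covariates.** In the second scenario that model would have about 69% power, but it is not planned. The working-memory stratum already recovers part of the precision, so 74–80% is the fair start.
- **That the gain is large whatever r is.** At r = 0.3 it is 0 to 2 percentage points.
- **That a chance baseline gap passes in full into the primary estimate.** Only the fraction given by the baseline-outcome slope does, and the planned standard error already covers that variation.
- **That the MRI analyses ignore the baseline scan.** The fMRI ANOVA has time as a factor, and the Sample size section defines the BOLD measure as a change from before the intervention. For the diffusion metrics the text is unclear on whether change is meant.
- **That every child certainly has a baseline score.** The assessment is planned for all participants, but some scores may be missing.

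**Conclusion.** The point holds as a recommendation on efficiency. The primary model leaves out a pre-randomisation measurement of the primary outcome that is already planned for all participants, in a trial with little scope to add children. At the protocol's 63 per arm, including it adds about 0–2 points of power at r = 0.3, 4–7 at r = 0.5 and 9–14 at r = 0.7. In the scenario with loss and sibling clustering, the gains are about 0–2, 5–9 and 14–19 points, and at r = 0.5 or above power exceeds 80% throughout the range.

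These sizes rest on an assumed r, on the Background correlations carrying over to this subtest and this outcome, on the stratum relating equally to both WRAT-4 scores, and, in the second scenario, on the assumed 15% loss and ICC of 0.5. The direction of the point does not depend on them; the amount does. The imbalance-triggered covariate choice is a weakness at any r.

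**What to change.** In the primary GEE model, prespecify the child's baseline score on the same WRAT-4 subtest as a covariate alongside the two stratification factors. State a simple rule for missing baseline scores, such as imputing the mean over both arms, so that no randomised child with an outcome is lost.

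Do the same for the other continuous outcomes measured at baseline: working memory, attention, processing speed, SDQ and BRIEF. For the diffusion metrics, add the pre-intervention value unless they are already analysed as change. The BOLD analysis needs no alteration.

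Replace the imbalance trigger with a short list of prognostic covariates, fixed now and drawn from data already collected, such as baseline GCA from the DAS-II.

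The cost is a few sentences in the analysis section or SAP. No new data are needed, and the sample size can stay as it is.

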School-aged EPT children perform more poorly on measures of working memory and are at greater risk of exhibiting working memory deficits than their term-born peers [15-21]. As is the case in the general population, working memory has also been associated with academic performance in VPT children. Mulder and colleagues reported high correlations between verbal working memory and academic achievement in VPT children, with correlation coefficients ranging from 0.42 to 0.61 [22]. The association between working memory and academic achievement is particularly pertinent in the VPT/EPT population as it is well established that these children perform poorer on measures of basic academic skills, have elevated rates of academic underachievement and grade retention, and use more educational remediation services than term born children [4,23,24]. For example, a recent meta-analysis of 14 studies reported that VPT or very low birthweight (VLBW) children score on average 0.5 SD lower on tests of reading, 0.8 SD lower on tests of spelling, and 0.6 SD lower on tests of mathematics compared with term children [25]. These difficulties are even more prominent in children born at earlier gestational ages and with lower birthweight. It has been shown that 11-year- old EPT children score on average 1 SD below term peers on reading tests and 1.5 SD below on measures of mathematics, with 52% of EPT children classified as reading impaired and 70% as mathematically impaired [23].

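### The main model for continuous outcomes, including 24-month WRAT-4, leaves out the child's own baseline score, giving up precision and protection against chance imbalance

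*Protocol article*

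**What the plan says.** The Statistical analysis section gives one main model for all continuous outcomes: "linear regression adjusted for stratification factors of multiple births and low/normal working memory capacity at baseline". It is fitted by GEE with sandwich standard errors so that twins and triplets are handled as clusters. Other baseline factors enter only in a sensitivity analysis, and only where the arms turn out to differ by chance.

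The working-memory factor is defined under Randomisation. It is a single subtest, Backward Digit Recall, split at the 20th percentile, with about 40% of children expected in the low group.

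Table 1 marks a baseline assessment for the primary measure, "Wide Range Achievement Test-4th edition (WRAT-4", and for the WMTB-C, AWMA, TEACh, CogState, SDQ and BRIEF. Its footnote says of the timing: "Neuropsychological measures and behavioural questionnaires at the baseline time-point were completed prior to enrolment into the trial". The Procedures and measures section counts academic skills within the neuropsychological assessment, so the footnote covers the WRAT-4.

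The Sample size section plans to detect a difference "of 0.5 SD in the intervention compared with the placebo group, with 80% power and a type-I error rate of 5" per cent, with 63 children per arm.

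**The concern.** A child's earlier score on the same attainment test is normally a strong predictor of the later score, and this trial holds that score before treatment starts. The main model replaces it with a two-level cut of one working-memory subtest, which is a different construct measured coarsely.

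Two things follow, and they are two views of one loss. Outcome variance that could be explained stays in the residual, so the confidence interval is wider than it need be. In any one realised trial, part of a chance difference in baseline attainment also remains in the estimated effect. This matters more here because the Statistical analysis section says results will be read by the size of the group difference rather than by significance alone.

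**Working it through.** **Inputs from the protocol article**
- Sample size: 63 per arm, target 0.5 SD, 80% power, 5% type I error.
- Primary outcome: WRAT-4 scales have SD 15, so 0.5 SD is 7.5 points.
- Randomisation: about 40% of children classed as low working memory.
- Background: verbal working memory and achievement in very preterm children have "correlation coefficients ranging from 0.42 to 0.61".

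**Assumptions**
- The correlation r between baseline and 24-month WRAT-4 is not in the documents. I use 0.5 to 0.8.
- The Background correlations apply to Backward Digit Recall and the WRAT-4.
- The working-memory stratum relates to baseline WRAT-4 as it does to the outcome.
- Clustering of multiples, dropout and any contribution from the multiple-birth factor are ignored.

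**1. The plan's own figure.** n per arm = 2(1.960 + 0.842)² / 0.5² = 62.8, so 63. Power at 63 per arm is 80.1% by the normal approximation and 79.5% by the noncentral t. The stated sample size reproduces as an unadjusted, two-sided calculation.

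**2. What the working-memory split explains.** Cutting a normal variable 40/60 keeps φ(z₀.₄)/√(0.4 × 0.6) = 0.386/0.490 = 0.789 of its correlation. The split then correlates with the outcome at d = 0.42 × 0.789 = 0.331 to 0.61 × 0.789 = 0.481. It explains d² = 11% to 23% of the variance.

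**3. The stated model.** Residual SD = √(1 − d²) = 0.944 to 0.877. Power for 0.5 SD is 84% to 89% (noncentral t, 63 per arm).

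**4. Adding the baseline score.** With the split kept in, R² = (r² + d² − 2rd²)/(1 − d²), the residual SD is √(1 − R²), and the interval narrows by 1 − √(1 − R²)/√(1 − d²).

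| r (assumed) | Residual SD, d = 0.331 / 0.481 | Power for 0.5 SD | Interval narrower by |
|---|---|---|---|
| stated model | 0.944 / 0.877 | 84-89% | – |
| 0.5 | 0.848 / 0.821 | 91-92% | 6-10% |
| 0.6 | 0.788 / 0.769 | 94-95% | 12-17% |
| 0.7 | 0.706 / 0.695 | 98% | 21-25% |
| 0.8 | 0.596 / 0.590 | over 99% | 33-37% |

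**5. Chance imbalance left by the stated model.** The standard error of the within-stratum baseline gap is √(2/63) × √(1 − d²) = 0.178 × 0.944 = 0.168 SD, or 0.178 × 0.877 = 0.156 SD. The chance of a gap of at least 0.2 SD (3 points) is 2[1 − Φ(0.2/0.168)] = 23%, or 2[1 − Φ(0.2/0.156)] = 20%.

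The share of a gap that reaches the estimate is (r − d²)/(1 − d²). At r = 0.5 it is 0.35 to 0.44, so a 0.2 SD gap carries 0.07 to 0.09 SD. At r = 0.8 it is 0.74 to 0.775, so the same gap carries 0.15 to 0.155 SD. In WRAT-4 points this is about 1.0 to 2.3, against a target of 7.5.

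**The case against.** The plan is defensible as it stands. Adjusting for stratification factors is standard, randomisation keeps the estimate unbiased on average, and the confidence interval already allows for chance baseline differences. On these assumptions the stated model exceeds the planned 80% power before clustering and dropout. A prespecified sensitivity analysis can also bring in baseline WRAT-4 if the arms differ on it. All of this stands, and it makes the point one of efficiency. The sensitivity analysis is only a partial answer: observed imbalance triggers it, and it leaves the headline estimate unchanged.

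The size of the gain rests on a correlation the documents do not give. The Background correlations are for verbal working memory in very preterm children; they are not stated for this subtest, for the WRAT-4 or for a 24-month interval. This also stands. At r = 0.5 the gain in power is only about 4 to 7 percentage points.

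A reader might work out the imbalance as if nothing were adjusted: a 26% chance of a gap of 0.2 SD or more, with r times the gap (0.12 to 0.16 SD for r = 0.6 to 0.8) carried into the estimate. The documents do not support that reading, because the stated model already adjusts for the working-memory stratum. Step 5 gives the figures that apply.

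**Conclusion.** The point holds as a recommendation on precision. The article names the covariates of the main model, so this is not a detail left open for a later plan, and a baseline measure that is already collected goes unused. The direction of the gain is close to certain. Its size runs from modest at r = 0.5 to large at r = 0.8 and depends on the assumptions listed in the working. Clustering and dropout would lower the absolute power of both models.

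Three stronger readings might be inferred and should not be:
- **The headline estimate is biased.** Randomisation rules this out on average; the issue is imbalance in the one trial that is run.
- **The sample size is wrong or the trial is underpowered because of this choice.** The 63 per arm reproduces, and the stated model does better than the unadjusted calculation behind it.
- **Imbalance is a second harm on top of the wider interval.** It is the same loss seen from another side.

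The point does not reach measures with no matching baseline, such as the Intrinsic Motivation Inventory, or the fMRI model, which already includes time.

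**What to change.** In the Statistical analysis section, make the main model for the WRAT-4 and for each other continuous outcome measured at baseline:

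follow-up score = arm + continuous baseline score on the same measure + multiple birth + working-memory stratum, fitted by the same GEE.

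State that children with a missing baseline score are kept, by mean imputation or a missing indicator. The documents give no count of missing baselines. Teacher ratings may be missing more often, because the Recruitment section makes them depend on consent from the parent, the principal and the teacher. Report the strata-only model as a sensitivity analysis.

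The cost is one degree of freedom per model (one more where a missing indicator is used) and a short change to the text. No new data, visits or children are needed.
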